### Clinical Data

Clinical data from the patients will be obtained by medical staff and recorded on an online electronic platform (http://www.medresman.org.cn) and in the CRF table. The samples will be coded, and the patients’ identity will be known only by the attending physician. The clinical data will include the following: general patient information, past medical history, past surgical history, laboratory examination results, imaging results, surgery details, PFS and OS. The timing and processing of the above recorded contents will be reflected in the CRF table, and the laboratory examinations will mainly assess preoperative and postoperative routine blood, liver function, tumor markers, and inflammatory indicators. The prognosis of GC with liver metastasis (GCLM) was very poor, with a 5-year survival rate of <10% (17). Patients will be assessed at least monthly from baseline for adverse events *via* verbal interview, physical examination, and blood tests, including a complete blood cell count and assessments of liver and renal function, until disease progression. Abdominal CT and measurements of tumor markers, such as carcinoembryonic antigen, carbohydrate antigen 199, carbohydrate antigen 125, carbohydrate antigen 153 and alpha fetoprotein, were done every 3 months.

A detailed description of the above data is shown in the CRF table. **Table 3** shows the test and data acquisition schedule for this experiment.

**Table 3 T3:** The test and data acquisition schedule for this experiment.

Stage	Pre-operation	Intra-operation	Postoperation					Unplanned follow-up
Follow up period	14-1 days		0-12 month	13-24 month	25-36 month	37-48 month	49-60 month	
Baseline data collected	√	—	—	—	—	—	—	—
Inclusion and exclusion	√	—	—	—	—	—	—	—
Sign informed consent	√	—	—	—	—	—	—	—
Group determination	√	—	—	—	—	—	—	—
Fill in the basic information	√	—	—	—	—	—	—	—
Physical examination	√	—	√	√	√	√	√	—
Imaging examination	√	—	√	√	√	√	√	if necessary
Laboratory examination	√	—	√	√	√	√	√	—
Operation information	—	√	—	—	—	—	—	—
Postoperative pathology	—	√	—	—	—	—	—	if necessary
Safety observation	√	—	√	√	√	√	√	if necessary
Record adverse events	√	—	√	√	√	√	√	if necessary
Other works	√	√	√	√	√	√	√	if necessary

### Collection and Storage Management of Biochemical Specimens

For this study, blood samples, tissue samples of GC, and tissue samples of liver metastasis from the participants will be collected and subsequently tested by the laboratories and pathology departments. As previously reported (18), the collection and testing techniques for the above samples are quite mature. All blood samples will be destroyed after the test without preservation. GC specimens and liver metastatic tissue specimens will be sent to the pathological examination for timely preservation. They will be separated into cryopreservation tubes, and the separated tissues will be stored in liquid nitrogen tanks. They will be stored for five years and then destroyed six months after the end of the study.

### Evaluation of Technology Effectiveness

Contrast enhanced CT and tumor marker testing were performed in the first month after D2 gastrectomy and RFA treatment to evaluate the effectiveness of the technique and as a new baseline for future comparison. Every 2 to 4 months, additional CT examinations were performed to assess the progression of the disease. For patients who cannot be evaluated by enhanced CT, additional Hepatic contrast-enhanced ultrasonography, MRI or PET/CT can be used for further evaluation.

For the definition of effective rate of D2 gastrectomy, according to NCCN guidelines for diagnosis and treatment of gastric cancer, tumor clearance effectiveness is defined as that the tumor markers are not increased compared with the baseline data, and CT does not find the recurrence of new tumor or metastatic lymph nodes, or potential metastases in other parts and organs (19, 20).

For the definition of effective rate of RFA treatment, according to standardized terminology and reporting criteria for tumor ablation, technique effectiveness is defined as no evidence of residual tumor within 1 cm of the ablation defect; local tumor progression (LTP) is defined as any new peripheral or nodular enhancement within 1 cm or enlargement of the baseline ablation defect (21, 22).

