### Study Endpoints

In this study, the primary endpoint will be the OS. The secondary endpoints PFS and total complication rate. The total complications will include postoperative and chemotherapy complications. Postoperative complications were defined as events occurring within 30 days after the procedure, the severity of which was assessed by the ClavienDindo classification system (23, 24). Postoperative complications will include surgical site infection (SSI refers to the infection that occurs in the incision, deep organ or cavity during the perioperative period. It is mainly divided into superficial wound tissue infection, deep wound tissue infection and organ/cavity infection); anastomotic leaks and duodenal blow-out (identified clinically or radiographically); Chylous fistula (defined as milky white liquid in peritoneal drainage fluid after the start of enteral nutrition); respiratory complications (defined as clinical manifestation of pneumonia or bronchopneumonia confirmed by computed tomographic scan); and other complications (such as: delayedgastricemptying, intestinal obstruction, anastomotic and/or abdominal bleeding, abdominal abscess, pancreatic fistula, pancreatitis and so on.). Postoperative mortality was defined as all-cause death occurring within 30 days after the procedure. Chemotherapy complications refer to the side effects of chemotherapy, such as ototoxicity and nephrotoxicity. For those patients delayed postoperative systemic radiotherapy and/or chemotherapy after 4 weeks of surgery due to surgery and its complications, their clinical data were recorded in detail and analyzed by subgroup stratification.

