### Follow-up

When patients are discharged from the hospital, the first follow-up is to be performed on the 14th day after surgery. The patients will be given physical examination, imaging examination and laboratory examination to determine the postoperative complications of the patients during the follow-up period. The next chemotherapy plan will be formulated for the patients according to the above results. Physical examination and laboratory examination will be performed at least monthly on all enrolled patients. Imaging examinations will be performed every three months. The patients will be followed up by researchers every month to every 3 months. In addition to the above, the complications of chemotherapy will be examined. Recurrence, metastasis, death, and dates of patients will be recorded. The contents of each follow-up will be collated and combined. The follow-up contents will be recorded in **Table 3**.

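### The protocol gives two conflicting CT schedules for progression, one tied to a post-procedure baseline that only the surgical arm can have, so the PFS comparison can be biased by scan timing

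*Protocol article*

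**What the plan says.** Three sections of the protocol article and one table bear on when progression is looked for.

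- **Clinical Data:** abdominal CT and tumour markers, ending with "alpha fetoprotein, were done every 3 months". No arm is named.
- **Follow-up:** "Imaging examinations will be performed every three months". The sentence before it covers all enrolled patients. The section opens with a visit that only operated patients can have: "the first follow-up is to be performed on the 14th day after surgery". That visit includes imaging, and its stated purpose is to find postoperative complications.
- **Evaluation of Technology Effectiveness:** "Contrast enhanced CT and tumor marker testing were performed in the first month after D2 gastrectomy and RFA treatment". This scan serves to judge the technique and also "as a new baseline for future comparison". The next sentence is "Every 2 to 4 months, additional CT examinations were performed to assess the progression of the disease". The section then gives an ablation-specific rule: "local tumor progression (LTP) is defined as any new peripheral or nodular enhancement within 1 cm or enlargement of the baseline ablation defect".
- **Table 3 (Clinical Data):** the columns are pre-operation, intra-operation and postoperation, the last in 12-month blocks. Table 1 shows that the control group has no operation.

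On the endpoint, Study Endpoints states: "The secondary endpoints PFS and total complication rate". OS is primary. The Discussion nevertheless names PFS beside OS as a main indicator of efficacy. Under Randomization Procedure, participants and clinicians are not blinded.

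**The concern.** Radiological progression is dated by the scan that shows it, not by the day it happens. If two arms are scanned on different grids, their recorded PFS differs even when the treatments do not. A range of 2 to 4 months also leaves the timing of each scan to clinicians who know the allocation.

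The reference scan raises a second issue. In the surgical arm, later scans are to be compared with a CT taken after the procedures. The article does not say whether a lesion that appears between randomisation and that CT is a PFS event or becomes part of the reference. Controls have no such reset.

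At stake is the credibility of the PFS result, which the Discussion treats as a main efficacy indicator.

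**Working it through.** **1. The text side by side**

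| Section | Interval | Counted from | Arm |
|---|---|---|---|
| Clinical Data | 3 months | not stated for CT | not separated |
| Follow-up | 3 months | not stated for imaging | not separated |
| Evaluation of Technology Effectiveness | month 1, then 2 to 4 months | the procedures (month 1); not stated for later scans | not named; context is the surgical arm |
| Table 3 | none given | the operation | columns fit the surgical arm only |

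The intervals do not agree, and no section says which governs PFS. The plan gives no figure for PFS, so there is none to reproduce.

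**2. Size of the timing shift by hand**

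Inputs: exponential true PFS with median m, equal in both arms; progression dated at the next scan on a grid of width w. The median is an assumption, since the document gives none. With hazard λ = ln 2 / m, the mean recorded time is w / (1 − exp(−λw)).

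For m = 6 months, λ = 0.1155:

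- w = 3: 3 / (1 − 0.7071) = 10.24 months
- w = 4: 4 / (1 − 0.6300) = 10.81 months, a shift of +0.57
- w = 2: 2 / (1 − 0.7937) = 9.69 months, a shift of −0.55

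A 4-month grid against a 3-month grid thus dates progression about half a month later, and a 2-month grid about half a month earlier, with no treatment effect. The simulated shifts at this median were +0.52 and −0.59.

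**3. Effect on the hazard ratio and false positives**

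Simulation: true hazard ratio 1, control CT every 3 months, censoring at 36 months. Hazard ratios (surgical versus control) come from a Cox model with Efron ties and 40,000 per arm. Rejection is by the log-rank test at 5% with 100 per arm and 400 replicates.

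| Surgical-arm CT | HR, median 4 / 6 / 9 months | Rejection, median 4 / 6 / 9 months |
|---|---|---|
| every 3 months (same grid) | 1.01 / 1.01 / 1.01 | 4.8% / 5.8% / 5.8% |
| every 4 months | 0.88 / 0.93 / 0.96 | 30% / 15% / 6% |
| every 2 months | 1.11 / 1.07 / 1.05 | 22% / 15% / 9% |
| month 1, then every 4 months | 0.96 / 0.96 / 0.96 | 12% / 8% / 6% |
| month 1, then every 3 months | 0.94 / 0.95 / 0.96 | 11% / 7% / 5% |
| month 1, then every 2 months | 1.11 / 1.07 / 1.04 | 24% / 15% / 9% |

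The simulation error of a rejection rate is √(0.05 × 0.95 / 400) = 1.1 points near 5% and √(0.15 × 0.85 / 400) = 1.8 points near 15%. A run with 1,000 replicates gave 12% (every 4 months) and 11% (every 2 months) at median 6, so the 15% entries lie at the upper end.

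A repeat over medians of 4 to 8 months gave Cox hazard ratios of about 0.87 to 0.96 with 10% to 29% rejection for fixed 4-month scans. Fixed 2-month scans gave about 1.02 to 1.10 with 7% to 21%.

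**4. Milder readings**

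- Interval varying uniformly between 2 and 4 months in the surgical arm: HR 0.97, 0.95 and 0.99, with rejection 10%, 5% and 6%, at medians 4, 6 and 8.
- The common 3-month grid plus one month-1 scan: rejection between 3% and 7%.

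**5. The baseline reset**

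Its effect depends on how many patients progress before the post-procedure CT and on how that CT is counted. The document gives neither, so no figure is put on it.

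**The case against.** The strongest reply is that no arm-specific interval is written down. The 2-to-4-month sentence names no arm, the two 3-month statements cover patients in general, and 2 to 4 is centred on 3, so it may be a window around the same rule. This stands. It turns the point into a conflict that can cause bias, and does not show that the arms are scanned differently. The conflict remains on either reading, because no section calls the range a window.

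A reader might go further and infer that PFS is biased in favour of surgery. The text does not support that. The direction reverses between 2-month and 4-month scans, and the larger effects need every surgical patient to be scanned at one extreme throughout.

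A reader might also quote hazard ratios as far from 1 as 0.79 or 1.20. Those come from a one-step log-rank estimate, which exaggerates the effect when many event times are tied. The Cox model gives the narrower range above. The raised rejection rate at the extremes does not depend on that choice.

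Third, a post-procedure reference scan is to be expected, because resected and ablated lesions cannot be followed against pre-treatment measurements. The same section also looks for new tumour, nodes and metastases on CT. It is therefore supposition that early failures are absorbed into the baseline. What stands is that the article sets a new baseline and leaves its role in PFS open.

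Finally, the day-14 visit is for postoperative complications, so it is weak evidence of an extra look for progression. Table 3 is a condensed calendar and does not define a PFS clock. A time origin or censoring rule may sit in a document not shown, and its absence is not counted here.

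**Conclusion.** The point holds as a conflict between sections with a possible effect on PFS. Clinical Data and Follow-up give 3 months. Evaluation of Technology Effectiveness gives 2 to 4 months and a reference scan without a control-arm counterpart.

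If that schedule is used in the surgical arm only, scan timing alone can raise the false-positive rate well above 5% at the fixed extremes, in either direction. It does little harm when both arms are scanned close to every 3 months. The sizes rest on assumed exponential PFS with medians of 4 to 8 months, 100 per arm and scans exactly on schedule. Possible loss of early events through the new baseline is a separate, unquantified risk.

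OS does not depend on scan dates and is unaffected. The change should be made, but it is not critical to the primary analysis. Confidence is medium, because the arm-specific reading is inferred from the section's heading and the sentence before it.

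**What to change.** Reconcile Clinical Data, Evaluation of Technology Effectiveness, Follow-up and the operation-based columns of Table 3 to one progression-imaging schedule. It should be the same in both arms and counted from randomisation. The interval is for the sponsor to choose; if 2 to 4 months is meant as a window around a 3-month visit, say so and apply it to both arms.

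Use the post-procedure CT as the reference for technique effectiveness and local ablation follow-up only. State that new lesions or progression seen on it count as PFS events.

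In the simulation, a common 3-month grid brought the hazard ratio to 1.01 and rejection to 4.8% to 5.8%, which is nominal within simulation error. The cost is wording, a revised Table 3 and less freedom in scan timing.

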To verify the comparison of the efficacy of D2 gastrectomy plus liver radiofrequency plus postoperative chemotherapy versus chemotherapy alone for patients with GCLM, we designed a superiority study with a superiority margin of 5% (α= 0.05, β= 0.20, 80% power). With a standard error of 0.05 and a confidence interval of 80%, a sample size of 178 is necessary. To minimize sampling error and account for the rate of loss to follow-up for various reasons, we determined the sample size to be 200 participants. Standard descriptive statistics will be used to analyze qualitative and quantitative variables such as relative and absolute frequencies, frequency tables, means, medians, standard deviations, ranges, and quartiles. A 95% confidence level will be considered appropriate for analysis. Descriptive statistics will also be used to describe the most relevant clinical parameter measurements. Analysis of categorical variables will be performed by two-sample t tests or Fisher’s exact test. If there is no significant difference in the response rate to D2 gastrectomy plus liver radiofrequency plus postoperative chemotherapy versus chemotherapy alone, then the result will be negative, that is, the difference is not related to whether to apply the treatment strategy of D2 gastrectomy plus liver radiofrequency plus postoperative chemotherapy for patients with GCLM; otherwise, there is a relationship.

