### Inclusion Criteria

Patients will be included when they meet all of the following conditions:

- Patients who are male or female, aged 20 to 75 years;- Patients who were diagnosed histologically with primary gastric adenocarcinoma;- Patients diagnosed with clinical T1–3 disease by laparotomy or laparoscopy (for T1-T3 patients with the node positive, in order to eliminate the inter group differences, they were randomly divided into control group or experimental group according to the clinical nodal status (further subgroup: N0–1 vs N2–3). For patients with para-aortic lymph node metastasis above the coeliac axis or below the inferior mesenteric artery (lymph node 16a1/b2 of maximum diameter ≥1 cm), or both, or T4 patients with the node positive, according to the NCCN diagnosis and treatment guidelines for gastric cancer and the recommendations of our multidisciplinary diagnosis and treatment team, neoadjuvant therapy was first chosen) (11);- Patients who will undergo diagnostic laparoscopic exploration combined with peritoneal lavage cytology to exclude peritoneal disseminated implant metastasis that is not visible to the naked eye (14);- Patients who will be examined for the molecular profile of the tumors (HER2, PDL1, MSI and MMR expression) [patients with HER2-positive advanced gastric cancer were excluded since trastuzumab in combination with chemotherapy has become the standard treatment for these patients (15)];- Patients with distant metastases that were limited to synchronous liver metastases confirmed by both laparotomy and CT scan;- Patients with metastatic liver tumor ranging from 2 to 4 with tumor diameters ranging from 1 cm to 5 cm (11) (In order to avoid the omission of potential liver metastases, we used contrast-enhanced liver ultrasound as one of the means of further screening. Considered that unless data are now available from ongoing trials, ablation for resectable liver metastasis lesions should not be used in radiofrequency of liver resection. We recommend all patients to multidisciplinary tumor boards to determine whether the liver metastasis is actually unresectable);- Patients whose PS (performance status) was from 0 to 1;- Patients who have not previously been treated for gastric cancer other than EMR;- Patients who have not previously received radiation therapy or chemotherapy for any other malignancy;- Patients who have no contraindications to treatment (surgery, radiofrequency ablation, and chemotherapy);- Patients and their families voluntarily participated in the study and signed the informed consent form.

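### The rule for the final conclusion rests on an undefined response rate, which contradicts overall survival as the primary endpoint; the same paragraph names t tests for categorical variables

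*Protocol article*

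**What the plan says.** Under Sample Size Estimate and Statistical Analysis, the article gives a rule for the final result. The condition is "If there is no significant difference in the response rate to D2 gastrectomy plus liver radiofrequency plus postoperative chemotherapy versus chemotherapy alone". If it is met, "then the result will be negative"; if not, "otherwise, there is a relationship". Shortly before the rule, the same paragraph says: "Analysis of categorical variables will be performed by two-sample t tests", with Fisher's exact test as the alternative.

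Under Study Endpoints the article says: "In this study, the primary endpoint will be the OS". It continues: "The secondary endpoints PFS and total complication rate". The abstract and the Main Objective section also make OS primary, and the Discussion calls OS and progression-free survival (PFS) the main indicators for comparing efficacy.

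**The concern.** A trial's decision rule should operate on its primary endpoint. Here the endpoint sections point to OS and the decision rule points to something else. A reader applying the rule would have to decide what response rate means, because the article does not say, and that choice could be made after results are known.

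The consequence is a wrong conclusion in either direction. The Discussion expects the result to bear on standard treatment for these patients, so the criterion on which success is declared has to be unambiguous.

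The t-test sentence is a separate, smaller error. A two-sample t test compares means and is not the method for categorical data.

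**Working it through.** The point is textual, so the check compares the relevant sections.

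**1. Where response rate appears.** It occurs once, in the decision rule. It is absent from the abstract's endpoints, Main Objective, Secondary Objectives and Study Endpoints. No section defines it.

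**2. What the endpoints are.**

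| Section | Primary | Secondary |
|---|---|---|
| Abstract (Methods/Design) | OS | PFS, complications |
| Main and Secondary Objectives | OS | PFS, complications |
| Study Endpoints | OS | PFS, complications |
| Decision rule | response rate | none named |

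**3. Whether another defined quantity could be meant.** Evaluation of Technology Effectiveness defines an effective rate for the D2 gastrectomy (markers and CT) and for the ablation (residual tumour near the ablation defect). Table 1 gives both procedures to the test arm only. Neither rate has a counterpart under chemotherapy alone, so neither can be the compared quantity.

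**4. Whether the sample size shows that OS was meant.** It does not. The inputs are adverse-event proportions of 60% and 81.8%, a 5-point superiority margin, α = 0.05 and 80% power, with a stated requirement of 178. The closest reconstruction is a one-sided comparison of two proportions with pooled variance:

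- mean proportion = (0.600 + 0.818)/2 = 0.709
- distance = 0.218 − 0.05 = 0.168
- n per arm = 2 × 0.709 × 0.291 × (1.645 + 0.842)² / 0.168² ≈ 90.4, rounded up to 91, so 182 in total

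This is close to 178 but not exact. The unpooled one-sided form gives 172, and the two-sided forms give 218 (unpooled) and 230 (pooled). None of these uses a hazard ratio, a median survival or a number of deaths. The sizing therefore gives no ground for reading response rate as OS.

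**5. What the rule does if followed literally.**

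| OS benefit | Response difference | Conclusion by the rule | Agrees with the primary endpoint? |
|---|---|---|---|
| yes | yes | relationship | yes |
| yes | no | negative | no |
| no | yes | relationship | no |
| no | no | negative | yes |

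In two of the four combinations the rule contradicts the primary endpoint.

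**The case against.** The strongest reply is that the article is condensed, that OS is plainly its primary endpoint, and that a fuller analysis plan may hold the survival methods. Part of this stands. The lack of a named log-rank or Cox method is not a finding here. But a plan that is not shown cannot remove a rule that the article itself states and that names a different variable. It could only conflict with that rule.

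A reader might go further in several ways that the text does not support:

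- **That OS plays no part in the trial's conclusion.** The Discussion names OS and PFS as the main efficacy indicators. Monitoring of the Study holds a second, interim rule based on superiority and significance. That rule names no endpoint, so it does not resolve the contradiction, but the final rule is not the only one.
- **That OS would be analysed by t test or Fisher's exact test, ignoring censoring.** Those tests are assigned to categorical variables. Fisher's test suits the complication rate. Their link to the response-rate rule is only an inference from adjacency.
- **That the power lost can be calculated by comparing Fisher's test on deaths at a fixed time with a log-rank test.** The article proposes no such analysis of deaths.
- **That the rule tests for exactly zero difference despite the 5% margin.** No null value is stated.
- **That surgery and ablation would mechanically produce a response difference.** This is plausible, but it presumes a lesion-based definition that the article does not give.

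**Conclusion.** The statement is wrong as written. The rule for the final conclusion uses a variable that is undefined and is not an endpoint, and so contradicts the declaration that "the primary endpoint will be the OS". This rests on the article's text alone and needs no assumed effect size. Its size is the two discordant outcomes out of four. How likely each is cannot be computed, because response is undefined and the article gives no assumed OS effect. The naming of two-sample t tests for categorical variables is also wrong, though less consequential.

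The supported conclusion is a contradiction between sections that must be resolved before any comparative analysis. It does not show that OS has been abandoned, or that survival data would be analysed by methods for categorical variables.

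**What to change.** Replace response rate with OS in the decision rule. Suggested wording: *The conclusion of the trial rests on the comparison of overall survival between the randomised arms by a log-rank test, with the hazard ratio and 95% confidence interval from a Cox model.*

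Stratify both by nodal status (N0–1 versus N2–3) if that factor was used in allocation. The Inclusion Criteria say that patients were "randomly divided into control group or experimental group according to the clinical nodal status", but only in a parenthesis about node-positive T1–T3 disease, and Randomization Procedure names no strata. Confirm which is correct before fixing the model. The article gives no division of the significance level between the interim and final analyses, so the rule should refer to whatever level the interim plan leaves.

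Compare complication rates by chi-square or Fisher's exact test, and delete the t test for categorical variables.

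The cost goes beyond wording. Terminating Study Criteria removes from the final analysis the data of patients who meet a termination criterion. That must be reconciled with an analysis of all randomised patients, and survival follow-up of those patients must continue after termination. If it has not been collected so far, it will have to be.
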